## **Quality assurance**

Both the research protocol and the informed consent were approved by an independent research ethics committee (CEI Campo Abierto Ltda, approval certificate No. 209, July 2024). All study participants signed the informed consent document before performing any research procedures.

## **Expected results of the study**

### **1. Contribution to the Advancement of Knowledge**

This study will contribute significantly to the field of music therapy in psychiatric settings, particularly in hospitalized patients with mental health disorders. The observed difference in stress reduction between the high and low frequency groups indicates that the intensity of music therapy may be a key factor in treatment efficacy. The association between positive expectations towards music therapy and greater symptom reduction offers a novel perspective on the importance of the psychological component in non-pharmacological treatments, suggesting that patient predisposition may influence therapeutic outcomes.

## **2. Application of the Results in Health Care**

The results of the study could encourage the integration of high-frequency music therapy sessions as a regular intervention in the treatment of hospitalized psychiatric patients, especially for those experiencing elevated levels of stress. This could improve current approaches to stress and anxiety management in this population group, helping to reduce reliance on anxiolytic or antidepressant medications in certain cases.

The observation that both groups experienced improvements in anxiety, depression, and life satisfaction supports the inclusion of music therapy, regardless of frequency, as a valuable intervention in inpatient treatment programs.

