## **Data Management and Statistical Analysis**

The sample size will be calculated with a power of 85% and a bilateral significance level of 0.05, aiming to detect a mean difference of 4 between experimental and control groups, with an estimated standard deviation of 5. A minimum sample size of 60 subjects (30 per group) will be targeted, with 35 per group to account for possible dropouts.

Data analysis will use Jamovi software, version 2.6 (2024). Descriptive analysis will characterize the sample, including central tendency and dispersion measures, and the normality of continuous variables will be assessed using the Shapiro-Wilk test. Differences between intervention and control groups will be determined using the Mann-Whitney U test for non-normally distributed data, and correlation analyses will use Spearman's nonparametric test where applicable. The analysis will include evaluations of sociodemographic and initial characterization variables, complemented by a correlation matrix for primary variables and outcomes.

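### The expected-results text supports music therapy at any frequency from improvement within both arms, which neither that observation nor the planned between-arm test can establish, and it also links anxiety to high frequency

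*Protocol*

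**What the plan says.** The hypothesis in the Protocol's Rationale & background information is that more frequent sessions do better on anxiety, depression, stress and life satisfaction alike. Study design makes depression, anxiety and stress jointly the primary outcome.

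Expected results of the study then words conclusions:

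- Item 1 (Contribution to the Advancement of Knowledge): "The observed difference in stress reduction between the high and low frequency groups indicates that the intensity of music therapy may be a key factor". The sentence goes on to speak of efficacy overall, not of stress.
- Item 2 (Application of the Results in Health Care), first paragraph, on adopting high-frequency sessions: "This could improve current approaches to stress and anxiety management in this population group".
- Item 2, second paragraph: improvement in both groups in anxiety, depression and life satisfaction "supports the inclusion of music therapy, regardless of frequency, as a valuable intervention in inpatient treatment programs".

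On inference, Data Management and Statistical Analysis says: "Differences between intervention and control groups will be determined using the Mann-Whitney U test for non-normally distributed data". The sample size rests on "a bilateral significance level of 0.05", 85% power, and "aiming to detect a mean difference of 4 between experimental and control groups, with an estimated standard deviation of 5". It does not name the scale to which the 4 points and the SD of 5 belong.

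**The concern.** The trial compares two frequencies, so its evidence on frequency is the difference between arms. The second paragraph of item 2 takes its frequency statement from another source, change within each arm. Both arms can improve whether the difference between them is zero, small or large.

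The between-arm test does not fill the gap. It is a test of difference with no margin, and a non-significant result would leave open effects as large as the one the trial was sized for.

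Anxiety also needs reconciling. One paragraph links it to a gain from high-frequency sessions. The next lists it among outcomes for which support is said to hold at any frequency.

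At stake is how the result will be read. A real frequency effect on anxiety or depression that the trial misses could be passed on as frequency not mattering there, and items 3 and 4 of the same section carry the findings to health systems and policy makers.

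**Working it through.** **Inputs.** From Data Management and Statistical Analysis: difference 4, SD 5, two-sided 0.05, power 85%, 30 per arm (35 with dropouts). From Participants: 91 expected to be randomised, about 45 per arm. Assumed here: SD 5 on each DASS-21 domain, normal data analysed by t-test, and a between-domain correlation of 0.3 to 0.7, which the Protocol does not give.

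**1. The plan's own figure.** n per arm = 2 × [(1.960 + 1.036) × 5/4]² = 28.06, so 29. The t-test version gives 29.05, so 30. The stated 30 per arm is reproduced, and power there is 86.1%.

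**2. What a non-significant result leaves open.**

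- SE = 5 × √(2/30) = 1.291; t(58, 0.975) = 2.002; half-width = 1.291 × 2.002 = 2.58 points.
- Non-significant if the observed difference is below 2.58. The interval still reaches 4 if the observed difference is at least 4 − 2.58 = 1.42.
- So an observed difference of 1.42 to 2.58 is non-significant and compatible with 4.
- The window narrows with more patients. At 35 per arm, SE = 1.195, t = 1.995 and half-width 2.39 (window 1.61 to 2.39). At 45 per arm, SE = 1.054, t = 1.987 and half-width 2.09 (window 1.91 to 2.09).
- A true 2-point effect has power 33% at 30 per arm, so it is missed 67% of the time on any one domain.

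**3. How often domains disagree by chance.** Simulated trials with the same true effect on all three domains, 30 per arm, each domain tested at two-sided 0.05. Ranges run over correlations 0.7 to 0.3.

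| True effect on every domain | Some but not all significant | Stress alone significant |
|---|---|---|
| 4 points | 21-31% | about 2% |
| 3 points | 36-57% | 6-8% |
| 2 points | 35-55% | 7-11% |

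At 45 per arm and 4 points, the mixed pattern falls to 7-10% and stress alone to about 0.5%. At 2 points the larger sample hardly helps: the mixed pattern is still 38-50% for correlations 0.7 to 0.5.

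**4. The two anxiety statements.** The first is about a possible gain from high frequency, which needs a between-arm difference on anxiety. Item 1 mentions such a difference for stress only. The second is about change within both arms. They can both be true if both arms improve and the high-frequency arm improves more, but then the any-frequency qualifier misleads for anxiety.

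**The case against.** The strongest reply is that the text claims less than a critic may hear in it. Several parts of that reply stand.

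- The wording is hedged (may, could). The Protocol does not assert that high frequency improves anxiety management.
- A reader might infer that the plan claims a stress-specific frequency effect. No section says so. Item 1 generalises from stress to treatment efficacy, and the contrast appears only when items 1 and 2 are set side by side.
- A reader might also infer that a non-significant between-arm test is being turned into equivalence, or that one session is called as good as five. The stated basis is improvement within both groups, and the sentence can be read as endorsing music therapy at either frequency.
- The two anxiety statements are not a strict contradiction, as step 4 shows.
- Stress significant alone is uncommon, and at the projected enrolment with a true 4-point effect even a mixed pattern is infrequent. It is a possible outcome, not the expected one.
- Confidence intervals, margins and contrasts are commonly left to an analysis plan, which is not at hand. Their absence from the Protocol is not the finding.

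The milder reading of the any-frequency sentence does not rescue it. Improvement in both arms is silent on frequency, yet the sentence brings frequency in and sets it aside. The lack of an arm without music therapy is a further problem for that sentence, but a separate one: the frequency statement would be unsupported even if both schedules were known to work.

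**Conclusion.** The point holds in a limited form. The Protocol words a conclusion on its own frequency question that neither within-arm improvement nor its difference test can deliver, and its two anxiety statements need reconciling. It also words results as already observed in a section on expected results.

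At the minimum sample size, observed differences of 1.42 to 2.58 points would be non-significant without excluding the planned 4. With equal true effects, mixed significance across domains would occur in roughly 21-57% of trials at 30 per arm for true effects of 2 to 4 points. These figures rest on SD 5 for every domain, normal data and correlations of 0.3 to 0.7. They show what could be misread and do not predict that it will be. The documents do not support saying that the plan sets out to report a domain-specific frequency effect or equivalence of the two schedules.

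**What to change.** **Expected results, items 1 and 2.** Delete the words *regardless of frequency*. Reconcile the two anxiety statements. Word results as conditional on what the trial finds.

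**Data Management and Statistical Analysis.** Add that:

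- every statement about frequency rests on the between-arm difference with its 95% confidence interval, for each DASS-21 domain and for life satisfaction;
- a non-significant difference is not worded as frequency not mattering;
- the 4-point benchmark is used only for the scale to which the sample-size assumption applies, and that scale is named;
- the frequency effect is called larger for stress than for another domain only if a direct contrast of the two arm effects, in the same patients and on a common or standardised scale, excludes zero. Even then, the contrast is not read as showing no effect in the other domain.

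**Cost.** Wording, and at most a few contrasts on data already planned; no extra patients or visits. The price is that a domain-specific or any-frequency conclusion will usually have to be weakened.

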## **Objectives and goals of the study**

### **General Objective:**

- To describe the response to high-intensity music therapy in hospitalized patients at the Montserrat Clinic.

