### **Specific Objectives:**

- To describe the sociodemographic and clinical characteristics of patients hospitalized with mental illness at Clínica Montserrat.
- To compare the levels of anxiety, depression, stress, levels of general life satisfaction and perception of the impact of music therapy. Before and after low and high intensity music therapy in patients hospitalized at Clínica Montserrat.
- To explore possible associations between sociodemographic and clinical characteristics of patients and their response to low-intensity versus high-intensity music therapy.

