## **Study design**

The study will be a randomized controlled clinical trial. Participants will be randomly assigned in a 1:1 ratio to either the high-frequency music therapy intervention group or the low-frequency control group. Randomization will be performed using random number generation. The high-frequency intervention group will receive five music therapy sessions over one week of inpatient treatment, at a rate of one session per day for five consecutive days. The low-frequency control group will receive one music therapy session in one week of inpatient treatment.

The primary outcome will assess symptoms of depression, anxiety, and stress during inpatient treatment. Secondary outcomes will include the perceived impact of the music therapy session on well-being and self-reported life satisfaction.

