## **Participants**

### **Inclusion criteria:**

- Individuals over 18 years of age.

- Psychiatric hospitalization of at least 48 hours at recruitment.
- Pharmacological treatment with medication adjustments in the last two weeks.

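### Improvement in both arms cannot support music therapy at any frequency: both arms receive it and every participant has recent medication changes, so only the high-versus-low difference supports an efficacy claim

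*Protocol*

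**What the plan says.** Under Expected results, subsection 2 (Application of the Results in Health Care), the protocol states: "The observation that both groups experienced improvements in anxiety, depression, and life satisfaction supports the inclusion of music therapy, regardless of frequency". The sentence carries no condition and ends in a recommendation for inpatient programmes.

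The Study design section sets out the two arms, allocated 1:1: "The high-frequency intervention group will receive five music therapy sessions over one week of inpatient treatment", and "The low-frequency control group will receive one music therapy session in one week of inpatient treatment". 

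The first list of inclusion criteria (Participants) requires "Pharmacological treatment with medication adjustments in the last two weeks". The second list (Population and Sample) has an equivalent requirement, and its population is patients in the clinic's intermediate or general psychiatry units.

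The general objective is "To describe the response to high-intensity music therapy in hospitalized patients" and names no comparator. The second specific objective compares symptom and satisfaction levels "Before and after low and high intensity music therapy in patients hospitalized".

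Data Management and Statistical Analysis plans a comparison between the groups (Mann-Whitney U for non-normal data) and sizes the trial on a between-group mean difference of 4 with SD 5.

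Problems anticipated lists self-report bias, the CISMA scale still being under development, lack of blinding and narrow diagnostic diversity. It mentions neither the absence of a group without music therapy nor the concurrent medication changes.

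**The concern.** The quoted sentence is a claim about music therapy against no music therapy. The trial contains no such comparison; it compares five sessions with one.

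If both arms improve, several explanations other than music are available, and the eligibility rules supply some of them: recently adjusted drugs and inpatient care for everyone. Natural recovery during the admission and regression to the mean add to these. Randomisation balances these influences between the arms, so they cancel in the high-minus-low difference. They do not cancel in the change within an arm.

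The sentence also fixes in advance how a null result will be read. If the arms do not differ, the trial has not shown that frequency matters and has not shown that either frequency works. Under this sentence the same result would be reported as favourable to both. The section on health policy implications then speaks of efficacy evidence that might lead policy makers to fund such programmes, so the claim is aimed beyond the clinic.

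**Working it through.** **1. What the design contrasts.**

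| Element | High frequency | Low frequency | Source |
|---|---|---|---|
| Music therapy in the week | 5 sessions | 1 session | Study design |
| Medication adjusted in the last two weeks | required | required | both inclusion lists |
| Psychiatric inpatient care | yes | yes | Population and Sample |

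Write the expected change in an arm as B + M, where B is the background change (drugs, care, recovery, regression to the mean) and M is the effect of music therapy at that arm's frequency.

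- High arm: B + M(5). Low arm: B + M(1).
- Difference: M(5) − M(1). B drops out because of randomisation.
- Change within either arm: B is still there, and nothing in the design estimates it.

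Improvement in both arms is therefore compatible with M(5) = M(1) = 0 whenever B is favourable.

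The Randomization section says that all subjects take part in both intensity modes. That contradicts Study design and the two must be reconciled, but on either reading nobody is observed without music therapy.

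**2. What the protocol powers.** Inputs from Data Management and Statistical Analysis: difference 4, SD 5, two-sided alpha 0.05, power 85%.

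n per group = 2(1.960 + 1.036)² × 5² / 4² = 28.06, rounded up to 29. The t-test solution is 29.05, rounded up to 30. The stated 30 per group reproduces. The stated 35 per group corresponds to 30 / (1 − 1/7), an implied dropout of about 14%. This calculation concerns the high-versus-low difference only. No calculation in the protocol addresses music therapy against none.

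**3. How often both arms would improve with no music effect (illustration).** Assumptions that are not in the protocol: M(5) = M(1) = 0; a common standardised background change d (mean change divided by the SD of change); a paired t-test in each arm at two-sided 0.05; independent arms.

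P(one arm) = P(T > t(0.975; n − 1)), where T is noncentral t with n − 1 degrees of freedom and noncentrality d√n. P(both arms) = P(one arm)².

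| n per arm | Basis | d = 0.3: one / both | d = 0.5: one / both |
|---|---|---|---|
| 30 | stated minimum | 36% / 13% | 75% / 57% |
| 35 | stated, with dropout | 41% / 17% | 82% / 67% |
| 45 | about half of the 91 projected to accept | 50% / 25% | 91% / 82% |

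Example at n = 35, d = 0.5: noncentrality 0.5 × √35 = 2.96, critical value 2.03, P(one) = 0.820, P(both) = 0.820² = 0.67.

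The result depends on d. At d = 0.2 the figure for both arms is only 3% (n = 30), 4% (n = 35) or 7% (n = 45). The quoted sentence speaks of improvement and not of significance, so the table shows the mechanism and is not a forecast.

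**The case against.** The strongest reply is that the planned analysis is sound on this point. The hypothesis is high against low frequency, the sample size is for that contrast, a between-group test is planned, and no paired or within-arm test is named. The sentence stands in a section on expected application, which governs neither conduct nor analysis. All of this is true. It means the analysis need not change and that the illustration above models a test the protocol does not plan. It does not rescue the sentence, which draws a conclusion that the planned test does not address. No analysis plan could repair it either, because the missing comparator is a matter of design.

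A reader might infer more, and the document does not support it:

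- *That the objectives themselves treat before-after change as proof of efficacy.* The general objective only describes. The second specific objective compares, and can be read as comparing change between arms.
- *That participants are newly admitted and at their worst.* The protocol does not say so. Its statements on length of stay at recruitment conflict with one another, and one passage gives priority to patients furthest into their stay.
- *That expectation is misread as a cause from a pooled correlation.* The protocol does not say whether correlations are pooled or by arm, and its wording is hedged: "suggesting that patient predisposition may influence therapeutic outcomes".
- *That the third specific objective is wrongly analysed.* It is exploratory. The analysis is "complemented by a correlation matrix for primary variables and outcomes", which is not declared to be the test for that objective, and interaction terms can be left to an analysis plan.
- *That the trial claims less medication, shorter stay or cost-effectiveness.* Those remarks are conditional and commit the trial to nothing.

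**Conclusion.** The point holds for the conclusion drawn under Application of the Results in Health Care. The trial can say whether five sessions differ from one. It cannot say that music therapy works at either frequency because both groups improved. This rests only on what the protocol states: music therapy in both arms, recent medication adjustment and inpatient care for all, and no qualification anywhere, including in Problems anticipated.

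The size can only be illustrated, because the protocol gives no background change. With no music effect and a within-arm test added, both arms would show significant improvement 13–17% of the time for a standardised change of 0.3 and 57–67% for 0.5 at the stated 30–35 per arm. At 45 per arm the figures are 25% and 82%. The inferential fault does not depend on these values.

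It should not be read as a fault in the planned between-group test or in its sample size, which reproduces.

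**What to change.** 1. Delete the sentence, or restrict it to what the high-versus-low comparison can show.
2. State that changes within an arm are descriptive and that efficacy conclusions rest only on the high-versus-low contrast.
3. Reword the general objective so that it names that contrast.
4. In Problems anticipated, add two limitations: no comparator without music therapy, and concurrent medication changes in all participants.

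The cost is wording; no data, visits or participants are added. The real price is that a null between-arm result can no longer be presented as support for music therapy.

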## **3. Impact on Health Systems**

Incorporating music therapy into inpatient programs for patients with mental disorders may offer a cost-effective therapeutic alternative and potentially reduce hospital stay or the need for additional interventions, which could optimize the use of resources in the health care system.

The use of an intensity-based approach to music therapy provides a basis for health systems to implement programs tailored to the needs and responsiveness of patients, thus maximizing the effectiveness of mental health interventions.

## **4. Potential Health Policy Implications**

This study could serve as a reference to guide mental health policies that include complementary therapies such as music therapy in psychiatric care protocols, recognizing the importance of non-invasive therapies in improving patients' well-being.

Evidence of the efficacy of music therapy in reducing stress and improving well-being could motivate policy makers to include and fund such interventions in hospitals and psychiatric facilities, promoting a holistic approach to mental health treatment.

## **5. Publications and Knowledge Dissemination**

The findings will be published in academic journals to inform the scientific community about the efficacy of different intensities of music therapy in psychiatric patients. In addition, it is expected that these results will be shared at mental health conferences and workshops so that professionals in the field can implement these approaches in their clinical practices.

Data on the relationship between expectations and intervention outcomes may provide a basis for future research on how psychological factors influence the effectiveness of nonpharmacological therapies, promoting a biopsychosocial approach to psychiatric care.

